## METHODS

2

### Study design

2.1

The aforementioned aims will be achieved in a randomized controlled trial with three parallel arms. Two smartphone application‐based interventions will be compared: a new intervention for reducing harmful drinking (Yoozan) and a control application (Yoozan without educational modules). Assessments will be completed at baseline, post‐assessment (30 days from registration), and follow‐ups at 60, 90, 120, 150, and 180 days (see Figure 1). The study was approved by the Hungarian Ethics Committee (2019/293). Consent is obtained electronically from all participants. The study is conducted in accordance with the Declaration of Helsinki.

**FIGURE 1 mpr1848-fig-0001:**
[figure not shown]
Overview of study design according to CONSORT format

### Recruitment of study participants and trial flow

2.2

Recruitment took place from December 2019 and is currently ongoing. Participants are recruited through promotion articles published on Hungarian Internet portals. In the articles, Yoozan is introduced with a call to participate in testing in case the reader wants to change his/her drinking habits. All interested participants are directed to the webpage of the study, from where the application can be downloaded. Based on a block randomization method, an equal number of participants download either Yoozan, the control application, or allocated to the wait‐list control group. After installing the application, participants are asked to read the participant information sheet and provide informed consent and a valid email address for which usability questionnaire and follow‐ups will be sent (see Figure 1).

Participants allocated to the wait‐list group are informed that 6 months later, the application will be sent to their email addresses and are encouraged to fill a few tests (7‐day Timeline Followback, Alcohol Use Disorders Identification Test [AUDIT]) with instant feedback.

Study inclusion criteria are informed consent via the Web form to ensure knowledge of procedures and the declaration of consent; participant age ≥18 years, to ensure a minimal age of participation; ownership of an Android‐operating smartphone and at least weekly Internet access, to ensure program access; a screening AUDIT score ≥8 out of 40, to include adults with potentially hazardous or harmful alcohol consumption; and an indication of an attempt to reduce alcohol consumption (screening motivation score ≥2 out of 5), to ensure a minimal willingness to change. Exclusion criterion is participation in other treatments for the reduction of alcohol consumption, to avoid confounding treatment effects.

The study targets Hungarian speaking users; thus, the language of the intervention is Hungarian. If the intervention is effective, translation to English and upload to App Store and Google Play is planned.

### Sample size calculation

2.3

Based on previous studies, realistic anticipation is a Cohen *d* of 0.20 for the effect size differences between the two study arms. To demonstrate standardized effect sizes, Cohens *d* of 0.20 with power (1−β) of 80% and an alpha of 0.05 in a two‐sided test performed with G*Power software (Faul, Erdfelder, Buchner, & Lang, 2009) 394 individuals would need to be included in each group. Based on the attrition rate of a self‐directed treatment‐seeker sample of Crane et al. (2018), we expect that 27% of study participants will respond to the first follow‐up, increasing the initial sample required by 3180; thus, we aim to recruit a total of 4356 participants.

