### Control application

3.5

The control application has the same core functions as Yoozan, without the educational modules. With the exception of WHO alcohol consumption guidelines, core functions do not contain explicit information on alcohol use. Thus, the rationale behind applying a control application was to investigate the effectiveness of the core functions in reducing alcohol consumption, without providing information on alcohol‐related topics.

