The following limitations of the protocol must be considered: (1) all measurements except behavioral data will be self‐reported that may be prone to biases (e.g., social desirability bias), (2) possible unequal group sizes leading to reduced statistical power due to the randomization process occurring before assessment for eligibility, (3) potentially there will be missing follow‐up data of the dropped outs, and (4) the application only available on Android operating smartphones.

Although mobile phones offer the potential to reduce the harms of hazardous drinking (Crane et al., 2015), up to date there have been relatively few studies conducted that evaluate the efficacy of evidence‐based smartphone applications aiming to reduce alcohol consumption (e.g., Crane et al., 2018; Gonzalez & Dulin, 2015; Zhang et al., 2016). By applying a randomized controlled trial, the results of the present study will be comparable with previous studies and will be informative about the overall efficacy of alcohol intervention applications. By investigating the behavioral correlates of the application, we hope that a more complex understanding of application efficacy will be achieved, making more focused intervention development possible in the future.

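### The recruitment total of 4356 is built on 392 per group rather than the stated 394, and the 80% power is shown only for one unnamed two-arm contrast at day 30

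*Protocol article*

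**What the plan says.** Section 2.3 (Sample size calculation) takes a Cohen d of 0.20 "for the effect size differences between the two study arms", with power "of 80% and an alpha of 0.05", two-sided, and concludes that "394 individuals would need to be included in each group". For attrition it says "we expect that 27% of study participants will respond to the first" follow-up, and gives the consequence as "increasing the initial sample required by 3180; thus, we aim to recruit a total of 4356 participants".

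Other sections set the scope that this calculation has to serve:

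- Section 2.1 describes three parallel arms, and Section 2.2 allocates them in equal numbers.
- Section 2.4 identifies the first follow-up as day 30. Section 2.1 adds visits at days 60, 90, 120, 150 and 180.
- The Introduction hypothesises lower consumption with Yoozan after the intervention and at every follow-up to day 180, compared with the control conditions. There are two of these: the control application and the wait-list.
- Section 3.5 says "The control application has the same core functions as Yoozan, without the educational modules".
- The Discussion lists, as a limitation, possible loss of power through unequal groups "due to the randomization process occurring before assessment for eligibility".

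**The concern.** There are two issues. First, the number per group, the increase and the total in Section 2.3 cannot all be right together, so a reader cannot tell which sample size was planned.

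Second, the power statement is narrower than the hypothesis. It covers one pair of arms, which is not named, at the visit to which the 27% applies. The efficacy hypothesis covers two control groups and visits to day 180. If the scope of the 80% is not written down, a null result at day 180, or against the control application, could be read as coming from a test known to have 80% power. The article does not show that it has.

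**Working it through.** **Inputs.** From Section 2.3: d = 0.20, two-sided alpha 0.05, power 80%, 394 per group, 27% response, increase 3180, total 4356. From Sections 2.1 and 2.2: three arms, equal allocation.

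**1. The plan's 394.** The normal approximation is n = 2 × ((1.960 + 0.842)/0.20)² = 392.44 per group. The two-sample t-test solution is 393.41, which rounds up to 394. The stated figure reproduces.

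**2. The total from 394.** 3 × 394 = 1182 and 1182/0.27 = 4377.8, so 4378, an increase of 4378 − 1182 = 3196. With each arm rounded up, 394/0.27 gives 1460 per arm and 3 × 1460 = 4380, an increase of 3198.

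**3. The base behind the printed total.** 4356 − 3180 = 1176 = 3 × 392, and 1176/0.27 = 4355.6, so 4356. The printed increase and total therefore both come from 392 per group. Adding 3180 to 1182 gives 4362, which is not the printed total either.

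**4. Size of the discrepancy.** 4378 − 4356 = 22 participants, about 0.5% (24 against 4380). At 4356 there are 1452 per arm, and 1452 × 0.27 = 392 responders. T-test power is 79.9% with 392 and 80.1% with 394.

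**5. Later visits.** The article gives no response rate after day 30, so the rates below 27% are assumptions. The setting is 1452 per arm, d = 0.20 and a simple t-test on that visit's responders. The last column is approximately 2.80 × √(2/n).

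| Response | Responders per arm | Power | d detectable with 80% power |
|---|---|---|---|
| 27% (stated, day 30) | 392 | 79.9% | 0.20 |
| 20% | 290 | 67% | 0.23 |
| 15% | 218 | 55% | 0.27 |
| 10% | 145 | 40% | 0.33 |

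A covariate-adjusted analysis can recover part of this. If covariates had a correlation of 0.5 with the outcome (assumed), power would be 0.90 at 27% response, 0.79 at 20% and 0.67 at 15%.

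**6. Yoozan against the control application, day 30.** With 392 per arm, power is 79.9% if d = 0.20. If the true d were 0.15 or 0.10 (assumed), it would be 56% or 29%. The Introduction's range of 0.20 to 0.42 is for digital interventions relative to control conditions. The article does not say why its lower end should hold against an application that shares all the core functions.

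**7. Who is counted.** If 4356 meant people allocated, and 20% or 30% of them proved ineligible (assumed), 392 × 0.8 = 314 or 392 × 0.7 = 274 per arm would remain, with power of 71% or 65%. If it means eligible participants, nothing is lost.

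**The case against.** The strongest reply is that little turns on the arithmetic: 22 people in more than four thousand, and power that still rounds to 80%. That stands, and it makes the first issue a correction of the text rather than a defect in the design.

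Four stronger readings are tempting, and the article does not support them.

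- **The trial lacks power against the control application.** At the stated d = 0.20 and equal allocation, that contrast has the same 79.9% at day 30 as the wait-list contrast. Since Section 2.1 speaks of comparing two applications, it may even be the pair that Section 2.3 means. The lower figures rest on effect sizes that appear nowhere in the article. What can be said is that d = 0.20 is not justified for this pair.
- **The trial is underpowered at day 180.** Later response is not given, and Section 4 plans a repeated-measures analysis with a mixed model for missing follow-up data, which may recover part of the loss. Neither the loss nor the recovery can be sized from the article. Nor does the article claim 80% at day 180; it ties the 27% to the first follow-up.
- **Ineligible participants erode the sample.** This holds only if 4356 counts people allocated. Participants recruited may equally mean those enrolled and eligible, and the Discussion already discloses that allocation comes first and may reduce power.
- **The primary engagement aim is unpowered.** No figure is printed for it, but a condensed article may leave that to fuller documents. With 2 × 392 = 784 responders in the two application arms, a correlation of about 0.10 is detectable, so no shortfall is shown.

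**Conclusion.** The point holds in a limited form. Section 2.3 contradicts itself: its increase and total belong to 392 per group, not 394. The consequence is about 0.5% of the sample and 0.2 percentage points of power.

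The 80% is supported for one unnamed two-arm contrast, at d = 0.20, at day 30. For later visits it is conditional on response staying at 27% or on the model making up any loss. For the control-application contrast at day 30 it is conditional on d = 0.20 applying there. Every figure given for lower response, smaller effects or ineligibility is illustrative and rests on a stated assumption. Severity is minor.

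**What to change.** - Make the figures agree. Either keep 4356 and state 392 per arm with 79.9% power, or keep 394 and state a total of 4378 (increase 3196), or 4380 with equal arms (increase 3198).
- Name the pair of arms and the visit to which the power applies. If d = 0.20 is meant for the control-application contrast as well, give the reason.
- Say that 4356 counts eligible participants, or state the allowance made for those found ineligible after allocation.
- Give the detectable effect at day 180 under an explicit response assumption, and say whether it refers to a simple comparison of responders or to the planned repeated-measures model.

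The cost is a few sentences in Section 2.3. Keeping 4356 requires no further recruitment; restating the total on 394 adds 22 to 24 participants. Design and analysis are unchanged.

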### Measures

2.4

At baseline weekly alcohol consumption, AUDIT score, motivation to change drinking habits, and sociodemographic data (age and gender) are assessed. Weekly alcohol consumption is assessed by the 7‐day Timeline Followback (e.g., see Sobell & Sobell, 1992) by users entering the consumption for each day of the previous week from a predefined list of drinks. It allows defining consumption measures that hopefully contribute better comparability between studies (Shorter et al., 2019), such as the frequency of drinking and heavy drinking (on a weekly level) and the summed consumption in standardized units. The AUDIT is a validated 10‐item screening tool developed by the World Health Organization (WHO) to assess alcohol consumption, drinking behaviors, and alcohol‐related problems. It is particularly designed for health care practitioners, but with suitable instructions, it can be self‐administered (Babor, Higgins‐Biddle, Saunders, & Monteiro, 2001). Motivation to change drinking habits is measured with the question “How important is it for you to change your drinking habits?” with five options to answer (1: not important, 5: very important).

The follow‐up questionnaires consist of the 7‐day Timeline Followback and application usability test. Subjective rating of application functions is measured at the first (30 days) follow‐up, with questions regarding the perceived effectiveness of each function helping to reach alcohol‐related goals, with five options to answer (1: very poor, 5: very helpful).

Besides the self‐administered tests, usage times of the application are recorded, and the following variables are formed: total usage, frequency (the number of usage sessions), and usage time of functions.

## INTERVENTIONS

3

### Educational application: Yoozan

3.1

The educational application, Yoozan, is a newly created smartphone application‐based intervention centered on Behavior Change Techniques (BCTs). BCTs are observable, replicable, and an irreducible component of an intervention designed to alter or redirect causal processes that regulate behavior (Michie et al., 2013). The motive during the selection of tools was to implement evidence‐based techniques to a mobile interface. Our work was not a pioneer in this respect; therefore, a relatively large body of evidence was available. The Drink Less application introduced by Garnett et al. (2016) used well‐reasoned modules in concordance with others (e.g., Attwood et al., 2017; Crane, 2017; Dulin, Gonzalez, King, Giroux, & Bacon, 2013), so we followed their work regarding the theoretical assumptions of the used functions. These are goal‐setting, self‐monitoring and feedback, action planning, normative feedback, and identity change (see Garnett et al., 2016). Based on the conclusion of Webb, Joseph, Yardly, and Michie (2010), by which the more BCTs were used in Internet‐based interventions, the more effective they were, additional functions were added to Yoozan. These are a chat room, providing peer support, evaluation of progress through achievements, and a state/mood‐activity diary. The state/mood‐activity diary was based on an extremely popular and well‐rated application, Daylio (Habitics, 2020; more than 5 million installs on Android, with an overall rate of 4.7 out of 5 based on more than 250,000 votes in 2020, Q2), the motive behind its use was twofold. On the one hand, based on the outstanding popularity of this formula, we anticipated that this tool would strengthen user engagement. Also, the state/mood‐activity data‐entry interface was developed in a way that it was only available once a user was done tracking the consumed drinks, serving as an additional motivation factor for tracking drinks. On the other hand, we assumed that tracking moods and activities might serve as valuable feedback, especially in relation to alcohol consumption.

The selection of tracked states was determined by states/moods known to be influenced by excessive alcohol consumption. A decrement in attention‐related cognitive abilities and memory functions are well documented in case of a hangover (e.g., Anderson & Dawson, 1999; McKinney & Coyle, 2004), thus a tracked state is (1) *intellectual sharpness*. Fatigue and a poor sense of well‐being are symptoms of a hangover (Wiese, Shlipak, & Browner, 2000), which is manifested in the state of (2) *energy level* and (3) *overall rating of the day*. Also, acute stress may produce an increase in alcohol consumption (de Wit, Söderpalm, Nikolayev, & Young, 2006), thus tracking (4) *stress level* in relation to alcohol consumption might help users to recognize a potential trigger of drinking. Also, Andersson, Söderpalm, and Berglund (2007) reported a positive relationship between reported stress reduction and the amount of alcohol consumed.

The application consists of three functional units: (1) registration and feedback, (2) core functions, and (3) educational modules (see Table 1 and Figure 2 for an overview).

**TABLE 1 mpr1848-tbl-0001:** An overview of the functions

Functional unit	Function	Rationale
Registration (present in Yoozan, control application and wait‐list groups)	Baseline tests (weekly alcohol consumption, AUDIT, and motivation to change)	Set pre‐intervention baseline
	Personalized feedback (weekly alcohol consumption and AUDIT)	Presenting drinking profile and normative comparison, as effective tools for reducing harmful alcohol consumption (Miller et al., 2013)
Core functions (present in Yoozan and control application groups)	Drink, activity, and mood diary	Providing a platform for clear, organized tracking of alcohol related data
	eBAC calculator	Calculating and displaying the estimated blood alcohol level
	Achievements	Creating goal commitment and providing additional feedback
	Role models	Promoting non‐problem drinking, harm reduction or abstinence
	Activity planner	Encouraging alternative activities other than alcohol consumption
	Community chat	Providing peer support
Modules (present only in Yoozan)	Module 1—consequences of excessive alcohol consumption and goal setting	Facilitating conscious evaluation of the effects of alcohol on ones' life
	Module 2—facilitate action planning and problem‐solving	Presenting a problem‐solving technique with practical information on how to prevent excessive alcohol intake
	Module 3—identify contextual factors and self‐control practices	Facilitating conscious evaluation of contextual factors related to excessive alcohol consumption
	Module 4—refusal skills training	Presenting communication techniques to help successful refusal of alcohol
	Module 5—relapse management	Presenting warning signs of relapse, action plans, and general information

Abbreviations: AUDIT, Alcohol Use Disorders Identification Test; eBAC, estimated blood alcohol concentration.

**FIGURE 2 mpr1848-fig-0002:**
[figure not shown]
An overview of the functions and navigation between functions

### Registration and feedback

3.2

The aim of the registration process is to collect baseline measures (weekly alcohol consumption, AUDIT, and motivation to change, see Table 2) and to provide feedback on the alcohol use of the participants.

**TABLE 2 mpr1848-tbl-0002:** Overview of the measurements

Measures	Baseline (t0)	Day 30 (t1)	180 days follow‐up (t2, t3, … t6)
Demographic (age and gender)	X	‐	‐
Demographic (level of education and place of residence)	‐	X	‐
7‐day Timeline Followback (Sobell & Sobell, 1992)	X	X	X
AUDIT (Babor et al., 2001). World Health Organization	X	‐	‐
Motivation to change	X	‐	‐
Usability ratings of the application	‐	X^a^	‐

^a^
Excluded in wait‐list control group.

Abbreviation: AUDIT, Alcohol Use Disorders Identification Test.

### Core functions of the application

3.3

Core functions include self‐monitoring (drink, mood, and activity tracking and feedback), estimated blood alcohol concentration (eBAC) calculator, role models, evaluation of progress (achievements), activity planner, goal‐setting, and community chat.

The *self‐monitoring function* can be divided into two functional units; data entry and feedback. Modern research on motivation reveals that persistence increases with the subjective proximity to goal attainment (Cheema & Bagchi, 2011; Louro, Pieters, & Zeelenberg, 2007), so we aimed to break the long process of cutting back or quit drinking into reasonable and achievable goals. Since health guidelines define the quantity of alcohol intake in weekly periods, the application was designed to focus users on this interval. According to this, the data entry interface is a modified calendar showing the current week and drinking‐related data of the user. The aim of the feedback page is to provide detailed information about the users' drinking habits, mood, and activities. Data is shown on various graphs, with the option to select and filter, to ensure in‐depth exploration (see Figure 3).

**FIGURE 3 mpr1848-fig-0003:**
[figure not shown]
Screenshots of the application: (a) data entry, (b) state/mood diary data entry, and (c) feedback of the tracked moods and alcohol consumption (translated from Hungarian to English for publication purposes only)

The *eBAC calculator* is a form of personalized feedback, an integral part of the Alcohol Skills Training Program (Fromme et al., 1994), calculating and displaying the estimated blood alcohol level of the individual, the excepted time it reaches zero and whether the user is allowed to drive.

Social control and social learning theories both emphasize the importance of *role models* in promoting non‐problem drinking, harm reduction, or abstinence (Moos, 2008). The role models function is a popup window appearing after opening the application, introducing a well‐known person (actor or singer), who successfully overcome his/her addiction.

Since gamification increases user activity (Juho, 2015), evaluation of progress is expressed through *badges, achievements, and trophies* to increase self‐efficacy and satisfaction, to create goal commitment, and to provide additional feedback. Achievements are divided into (1) *community achievements* where the summed outcomes (change in alcohol consumption, saved money, and avoided calories) of all users are displayed, and (2) *individual achievements*, which reflect the progress and goals of the individual user.

The idea behind the *activity planner* is that people tend to drink less during activities typically does not involve alcohol, for example, participation in volunteering is associated with less alcohol use (Weitzman & Kawachi, 2000). In Module 3, users could select the time periods they were engaged in heavy drinking, which are feedbacked as risky periods in the activity planner interface. Users are encouraged to set programs on those periods, either by adding their own ideas or by using a random activity generator.

The aim of the goal‐setting function is to facilitate goal statements regarding regulating alcohol consumption. Goal setting is an effective component of alcohol interventions (Tanner‐Smith & Lipsey, 2015), and the ability to set own drinking goals is highly valued by users (Giroux, Bacon, King, Dulin, & Gonzalez, 2014).

The aim of the *community chat* is to provide peer support. Peer support—the process of giving and receiving nonprofessional assistance from individuals with similar conditions—(Tracy & Wallace, 2016), is a key component of many existing addiction treatment approaches, such as the 12‐step programs (Allen, Anton, Babor, & Carbonari, 1997) or the community reinforcement approach (Meyers, Miller, Smith, & Tonigan, 2002). Online support groups also offer peer support, motivation, and positive role‐modeling (Moos, 2007). Based on Urbanoski, van Mierlo, and Cunningham (2016), relatively low activity is expected from most members but having an option for social networking might be a potential way to reduce attrition (Bennett & Glasgow, 2009). Community chat has six chat rooms with different topics: (1) successes, (2) lifestyle, (3), techniques (4), urgent (about to slip), (5) relapse, and (6) free. The rationale behind divide the chat into topics was to facilitate goal‐oriented communication between users.

